### Data management, safety, and monitoring

Study coordination and data management are based at Seattle Children’s Research Institute. Recruitment, survey, and intervention completion data for this study are collected and stored using REDCap [57], a Health Insurance Portability and Accountability Act (HIPAA) compliant platform managed by Seattle Children’s. Participant data are labeled using study identification numbers. Only study personnel with documented human subjects training and permission granted by the PI can access the database. Intervention sessions recorded for fidelity monitoring purposes are labeled with study identification numbers only and stored on password-protected secure servers at each site.

Per National Institutes of Health guidelines, a Data Safety Monitoring Board is not required given the early phase and minimal risk nature of this trial. The PI is responsible for all data and safety monitoring with support of the site PI and lead research coordinator. To ensure data quality, the PI conducts a weekly review of study databases, and staff review all surveys within 72 h for completion. The PI meets with the site PI and study staff at both sites weekly to review and discuss recruitment, data collection, and intervention delivery, and convenes quarterly meetings with an advisory committee, including the PRISM intervention developers ([name], [name]) and experienced behavioral intervention scientists. Any protocol deviations, instances of reportable new information (RNIs), or adverse events are recorded on standard forms and reported to the IRB of record for review. If any serious adverse events occur, these will be reported in writing to the IRB of record and the study sponsor and will trigger an immediate suspension of the research.

The PRISM-SN intervention addresses potentially sensitive subject matter. To ensure participant safety, PRISM coaches are trained to recognize signs of distress, concerning language, and potential for harm to self or others that may arise during sessions. If these instances occur, coaches are instructed to immediately notify the PI and the participant’s care team. Participants are informed that confidentiality may be breached in these instances. Given the early-stage nature of this trial, no interim analyses were planned.

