## Objectives and study design

This article describes the protocol of a pilot randomized-controlled trial (RCT) of the Promoting Resilience in Stress Management–Social Needs (PRISM-SN) adapted intervention among AYAs newly diagnosed with cancer**.** Our objectives are to assess the following: (1) feasibility, quantified via uptake, retention, and intervention acceptability; and (2) proof-of-concept, measured via minimal important difference on patient-reported outcomes (PROs) including SRCE (primary PRO of interest), social support, quality of life, hope, resilience, anxiety, and depression. For this pilot, parallel-group randomized trial, participants are randomized 1:1 to psychosocial usual care (UC, “control”) or PRISM-SN + UC (“intervention”) and complete PRO surveys at baseline and 12-week follow-up. We selected a pilot trial design with UC as our comparator to establish feasibility of delivering the PRISM-SN program in the context of a randomized trial and determine whether there is a signal of change in psychosocial outcomes in response to PRISM-SN compared to current standards of care. This protocol is reported following SPIRIT guidelines [55] adapted based on the CONSORT extension to pilot and feasibility trials [56] (Additional file 1).

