## Method

### Participants and procedures

Participants are recruited from two academic pediatric oncology centers in the United States: Seattle Children’s Hospital (SCH) and University of Pittsburgh Medical Center (UPMC) Children’s Hospital of Pittsburgh. To be eligible, AYAs must be 12–25 years old; diagnosed with a new malignancy treated with chemotherapy and/or radiation in the past 6 months; able to speak and read English; and cognitively able to complete the intervention and surveys. Concomitant psychological or psychiatric care and/or other psychosocial interventions are permitted during the trial, though AYAs may not have had previous exposure to or be co-enrolled in other studies of the PRISM program. Potentially eligible AYAs are identified by screening outpatient clinic and inpatient rosters, and eligibility is confirmed via electronic health record review. Eligible AYAs (and a parent or legal guardian, if < 18 years old) are then approached by study staff in person during a clinic visit or inpatient stay to introduce the study and obtain informed consent (AYAs ≥ 18 years old, parents of those younger) and written assent (AYAs 12–17 years old). Strategies to promote enrollment include utilizing in-person approaches; communicating with providers regarding ideal times for approach; and providing the option to complete consent conferences virtually/using electronic signatures after the initial in-person approach.

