Participant timeline is described in Fig. 1. Enrolled participants on both arms complete a survey containing a demographic questionnaire and a PRO battery at baseline (pre-randomization) and at 12-week follow-up. Surveys are administered via Research Electronic Data Capture (REDCap) [57] or paper and pencil upon request and must be completed within 4 weeks. Incentives of $25 and $50 are provided for baseline and follow-up surveys, respectively, and participants on both arms receive a small non-monetary incentive (e.g., tote bag or water bottle with the study logo) during their participation. To promote retention and follow-up, study staff contact participants via email, phone, or in-person check-ins to notify them of an upcoming survey due date and confirm how they would like to complete the survey (e.g., email link, study tablet provided during clinic visit, paper and pencil). Thereafter, staff provide weekly reminders for outstanding surveys. Clinical information is abstracted from electronic health records each month throughout the study period, including diagnosis, diagnosis date, treatment modalities and intensity, any pre-existing or current psychiatric diagnoses, and any formal psychological treatment received during study participation. Participants may be taken off study if they request to withdraw, do not complete study activities within the specified timeframe, are unable to be reached by study staff for > 4 weeks, or are deceased before completing study activities. For participants who request to withdraw from the study, study staff ask for and document reasons for withdrawal.

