### Intervention

#### Usual care

Participants randomized to both arms receive psychosocial usual care. At both sites, this includes an assigned social worker who conducts a comprehensive assessment at diagnosis and provides additional ad hoc services throughout treatment, with professional psychology services available upon family request or care team referral.

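### As worded, any serious adverse event, whatever its cause or arm, suspends the research, although the plan itself foresees inpatient stays, illness and death from cancer

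*Protocol article*

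**What the plan says.** The rule is in the protocol article, section Data management, safety, and monitoring. Adverse events in general are covered first: protocol deviations, reportable new information "or adverse events are recorded on standard forms and reported to the IRB of record for review". Serious events come next, and the trigger reads: "If any serious adverse events occur, these will be reported in writing to the IRB of record". The same sentence then names a second recipient of the report and ends with the consequence: "and the study sponsor and will trigger an immediate suspension of the research". The same section explains that no data safety monitoring board is required "given the early phase and minimal risk nature of this trial".

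Other sections describe who is at risk:

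- **Population** (Participants and procedures): patients "diagnosed with a new malignancy treated with chemotherapy and/or radiation in the past 6 months". They may be approached while admitted to hospital.
- **Death** (Participants and procedures): participants may be taken off study if they withdraw, cannot be reached, "or are deceased before completing study activities".
- **Setting** (PRISM-SN intervention): in-person sessions are arranged around clinic visits and hospital admissions.
- **Attrition** (Data analysis and sample size): 100 are to be recruited over 2 years, with a 30% allowance for losses that names illness and death among the causes.
- **Comparator** (Objectives and study design; Usual care): "participants are randomized 1:1 to psychosocial usual care" or to PRISM-SN on top of it. "Participants randomized to both arms receive psychosocial usual care", and the control arm gets no PRISM-SN session.

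**The concern.** The trigger is any SAE, the consequence is automatic, and it is immediate, so it comes before any judgement of cause. All adverse events already go to the IRB for review. Suspension is therefore an added step that does not wait for that review.

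In this population, serious events from the cancer or its treatment are foreseeable. In the usual-care arm they cannot be caused by PRISM-SN. After such an event the team has two options. It can stop recruitment and sessions in a minimal-risk psychosocial trial without a safety reason that concerns the intervention, or it can depart from its published safety rule. Neither is a good position, and a small change of wording avoids both.

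**Working it through.** **Step 1: the text.** The trigger was compared with every other statement in the article that could narrow it.

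- Relatedness: no limit is stated.
- Arm: no limit is stated, so usual-care participants are covered.
- Death as an individual reason to leave the study: this says what happens to the participant. It does not exempt the event from the trial-level rule.
- Harm arising in sessions: the later paragraph on coaches tells them to alert the PI and the care team. It does not redefine which SAEs suspend the research.

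These statements do not contradict the suspension clause. They show that background events are foreseen and that the clause, as worded, does not exclude them.

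**Step 2: the plan's own numbers.** With 70 evaluable and 30% attrition, 70 / (1 − 0.30) = 100 recruited, as stated. With 1:1 allocation, about 100 / 2 = 50 are in usual care. The article gives no SAE rate and no probability of suspension, so there is no further figure to reproduce.

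**Step 3: illustration.** Let p be the assumed risk that a participant has at least one SAE unrelated to PRISM-SN while on study, with participants independent. The chance of at least one suspension among n participants is 1 − (1 − p)^n.

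| Assumed p | All 100 recruited | 70 at risk | Usual-care arm only (50) |
|---|---|---|---|
| 0.1% | 9.5% | 6.8% | 4.9% |
| 0.5% | 39.4% | 29.6% | 22.2% |
| 1% | 63.4% | 50.5% | 39.5% |
| 2% | 86.7% | 75.7% | 63.6% |
| 5% | 99.4% | 97.2% | 92.3% |

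For example, at p = 1% and n = 100, 1 − 0.99^100 = 0.634. At p = 5%, 1 − 0.95^100 = 0.994, with 100 × 0.05 = 5 affected participants expected.

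**Step 4: what cannot be computed.** The article does not say how long a suspension would last or whether surveys would stop. At the planned pace of 100 / 104 weeks ≈ 0.96 enrolments per week, each week of pause would defer about one enrolment. The number of weeks is unknown, and deferred is not lost.

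**The case against.** The strongest reply is that the term is undefined here and may be defined narrowly elsewhere. The article defines neither an adverse event nor seriousness, and under Research ethics and dissemination it mentions a separate full protocol. Some of the text suits a study-related reading: death appears as an ordinary reason for one participant to leave, the monthly record abstraction does not list hospitalisations or toxicities, and the safety narrative concerns distress during sessions. Pausing on any SAE can also be defended as cautious in a trial with minors and no monitoring board, and the IRB approved the procedures.

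Part of this stands. A narrower definition may exist, and the practical consequence is operational. But the point is not that a definition is missing. The article states a complete trigger and a complete consequence, and the study-related limit appears nowhere in it. If that limit is intended, the published sentence needs the same correction. Caution is kept by reporting every SAE and by suspending for those possibly related.

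Three stronger readings are tempting, and the documents do not support them:

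- *A needless suspension is more likely than not.* A reader might infer this from the break-even risk, 1 − 0.5^(1/100) = 0.69%. That value holds for any 100-person study with an any-event rule. Without an SAE rate, the documents do not show that this trial lies above it.
- *The attrition allowance shows how frequent SAEs will be.* The 30% is not split by cause, and a participant can have an SAE without being lost.
- *Retention or the between-arm comparison would be damaged.* No suspension length is given, and no bias can be derived.

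**Conclusion.** The point holds as a badly fixed rule. The published sentence makes every SAE, in either arm and from any cause, suspend the research, in a population whose illness, hospital stays and deaths the plan anticipates. That conclusion rests on the wording alone.

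The size is illustrative. It assumes 100 participants, independence and a per-participant risk that the documents do not supply. The chance of at least one suspension unrelated to the intervention is then 63% at 1% and 99% at 5%, but only about 10% at 0.1%. The harm shown is interrupted recruitment and sessions, or departure from the stated rule. Nothing is shown about the trial's outcomes. The correction is worth making because it is cheap and gives up no SAE reporting.

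**What to change.** Keep written reporting of every SAE to the IRB and the sponsor, and replace the suspension clause with wording such as:

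*The research will be suspended automatically only for a serious adverse event judged at least possibly related to study participation, or when the IRB requires it. Deaths and hospitalisations attributed to cancer or its treatment will be reported without automatic suspension.*

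The condition should be relatedness alone. Requiring an event to be unexpected as well would narrow protection more than needed in a trial that includes minors and has no monitoring board.

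Cost: one sentence in the safety section, an IRB amendment, and a documented relatedness judgement for each SAE. If the full protocol already limits the rule in this way, bringing the published sentence into line with it is enough.

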### Research ethics and dissemination

A reliance agreement was established for the participating site to rely on the primary site’s IRB (Seattle Children’s Hospital); all study procedures were approved by the Seattle Children’s Hospital IRB (IRB00000277; IRB00009311). Any protocol amendments approved by the SCH IRB are communicated to the participating site via email; a shared study folder accessible by both sites is maintained by the lead research coordinator and contains all up-to-date study documents.

Study findings will be disseminated via publications and presentations at national and/or international meetings. Authors will include study investigators, collaborators, and staff; PRISM intervention developers; and members of the study advisory committee. The final study dataset will be de-identified and accessible to the PI and to trained study staff with IRB approval. Given the sensitive nature of the study population, participant-level data will not be made public to ensure privacy; any requests to use de-identified study data for secondary analyses must be submitted in writing to the PI and to the IRB for approval. The full study protocol and statistical code used in primary analyses may be published in public repositories per journal requirements.

## Discussion

This paper describes the protocol for a pilot randomized trial to demonstrate feasibility and proof-of-concept for the Promoting Resilience in Stress Management–Social Needs (PRISM-SN) intervention. PRISM-SN is an adaptation of an established psychosocial program [28, 43] including a new component designed to enhance social connection for AYAs newly diagnosed with cancer [51]. Anticipated outcomes from this study include feasibility, measured by uptake, retention, and intervention acceptability, and proof-of-concept, determined based on improvements in patient-reported social outcomes at 12-week follow-up.

This study has important strengths related to the intervention and study design. Leveraging an already established and successful program [43, 45, 46, 70], PRISM-SN applies a novel, developmentally informed, skills-based approach to target social connection, a previously unmet need for AYAs with cancer. In addition, the two-site pilot randomized trial design has the potential to provide stronger evidence of feasibility compared to smaller single-arm studies. This study will demonstrate the feasibility of delivering the PRISM-SN program; of recruiting and retaining AYAs in both the UC and intervention trial arms; and of implementing this protocol at multiple national sites. In addition, feasibility outcomes from this study will inform benchmarks for uptake, retention, intervention adherence, and data completion for a subsequent multi-site efficacy trial.

Limitations of this protocol should also be noted. First, generalizability may be limited by study sites and the patient populations they serve. Both sites are academic, pediatric-based AYA oncology centers who serve patient populations with limited racial and ethnic diversity. Subsequent trials of this program will need to recruit larger, more diverse samples and determine whether this protocol is feasible at community-based or adult AYA cancer centers. Second, PRISM-SN is only available in English; translation to other languages is an important future direction. Third, this pilot trial will not be powered to test whether delivery adaptations to promote accessibility (i.e., in-person vs. virtual sessions, combining modules) affect response to the program.

Future directions for this work include subsequent trials to determine whether PRISM-SN can improve social connection among AYAs in a large, diverse sample; examining psychosocial factors such as social anxiety that may influence response to the program; determining the added value of PRISM-SN compared to standard PRISM; examining implementation outcomes such as cost-effectiveness; and exploring the utility of the “Connecting with Others” skills for other populations or when combined with other supportive care programs.

Given the well-established risk for social connection deficits among AYAs with cancer and the limited availability of comprehensive interventions, novel programs including social health targets are needed. PRISM-SN has the potential to address this gap, enhance the comprehensiveness of the PRISM program, and improve overall psychosocial adaptation within the AYA oncology population.

## Data Availability

The datasets generated by this study will not be publicly available due to due to sensitive nature of the participant population and potential for individual privacy to be compromised but are available from the corresponding author on reasonable request.

## Abbreviations

AYA: Adolescent and young adult
PRISM: Promoting Resilience in Stress Management
PRISM-SN: Promoting Resilience in Stress Management–Social Needs
ORBIT: Obesity-Related Behavioral Intervention Trials
SRCE: Social Relationship Coping Efficacy
PRO: Patient-Reported Outcome
UC: Usual Care
REDCap: Research Electronic Data Capture
PROMIS: Patient-Reported Outcomes Measurement Information System
MCID: Minimal Clinically Important Difference
PHI: Protected Health Information
IRB: Institutional Review Board
